### Activity and Participation outcomes

#### Individual activity and participation based goals: *Canadian Occupational Performance Measure (COPM)* [46]

The COPM is the most frequently used measure of individual client centred outcomes in paediatric rehabilitation [47]. It measures individual, client-centred outcomes by focussing on the goals and priorities of the child and family [48]. The child-adapted model of the COPM will be administered via semi-structured interview with the parent/caregiver and child. Three sports related goals (at least one activity and one participation focussed) will be identified by caregivers. Ratings scale of their child’s performance and their satisfaction with this performance will be made on a 1–10 ordinal scale. The COPM has high re-test reliability (ICC 0.76–0.89). It demonstrates concurrent validity with the Functional Independence Measure and Klein-Bell [49] in addition to construct and criterion validity [50]. It has good sensitivity to change [49]. On the ordinal scale (1–10) a change of two or more points is considered clinically meaningful [51].

#### Functional Mobility and Balance: Timed up and go (TUG) [52]

The TUG is a simple measure of balance, anticipatory postural control and functional mobility. The modified procedure for children described by Williams et al. [52] requires participants to stand up from a chair with a backrest but no arms, walk three meters to touch a target before turning and returning to a seated position. They are timed from their bottom rising from the seat to touching back down on the seat and are given encouragement throughout the procedure. The TUG has a high within-session and test-retest reliability (ICC 0.99) [53]. It is reported to be an ecologically valid tool. The TUG is responsive to change over time in children with physical disabilities [52]. Minimal detectable changes of 1.4 s (GMFCS- E&R I) and 2.87 s (GMFCS- E&R II) have been calculated [54].

#### Gross Motor Capacity (CP Specific): Gross Motor Function Measure Challenge Module (GMFM Challenge) [55]

The GMFM Challenge was developed as an extension of the GMFM which is used internationally to quantify gross motor performance in children with CP. The GMFM can have a ceiling effect, especially for children of GMFCS- E&R I classification over the age of 5 years. The GMFM Challenge is an observational measure of high-level skills, speed and quality of performance in children with ambulatory CP. It has been found to have excellent inter-rater (ICC = 0.97) and test-retest reliability (ICC = 0.96) [56]. The content validity of the GMFM Challenge was enhanced by using existing, feasible and relevant observational gross motor measures, working with experienced clinicians and performing participant based content validity checking with children with CP. Rasch analysis has been completed but not yet published [57]. Preliminary minimal detectable change values have been reported at 7.17–8.44 [56].

#### Gross Motor Capacity (Sport Specific): *Test of Gross Motor Development-2 (TGMD-2)* [58]

The TGMD-2 is an observational measure of gross motor skill performance relating to sports. It assesses skills in two categories, locomotor and object control, each with six items. In doing this, the TGMD-2 focusses on specific sports skills and is often used for children in mainstream education or sporting contexts and has been reported to be the gold standard for gross motor skill for pre-schoolers [59]. It is reported to have high inter-rater, test-retest, internal and composite reliability [58, 60–62]. Ulrich [58] reports excellent validity and clinical feasibility in the TGMD-2 manual and studies have demonstrated construct validity [61] and concurrent validity with the GMFCS- E&R [62], Pre-schooler Gross Motor Quality Scale [59] and measures of physical fitness [63].

#### Participation Frequency and Enjoyment: *Children’s Assessment of Participation and Enjoyment (CAPE) and Preferences of Activities for Children (PAC)* [64]

The CAPE and PAC are questionnaires that measure participation of children in a range of activities outside of school. The CAPE-PAC measures who a child is participating with, enjoyment of an activity and the diversity and intensity of participation in formal (organised sport, other skill-based activities, and clubs, groups and organisations) and informal activities (recreational, active-physical, social, skill-based, and self-improvement). It has adequate test-retest reliability (ICC = 0.67–0.86) [65]. There is evidence for construct and face validity and clinical utility [65, 66].

### Contextual

#### Quality of Life: *Cerebral Palsy Quality of Life- children’s version (CP QOL-Child)* [67]

The CP QOL-Child is a quality of life questionnaire that assesses wellbeing in seven domains. It was specifically designed for children with CP aged 4–12 years. Parent proxy reports will be used in this study due to the age of most children anticipated in the *Sports Stars* group. The CP QOL-Child demonstrates high internal consistency (ICC 0.74–0.92) and test-retest reliability (ICC 0.76–0.89) for the parent proxy report. It demonstrates adequate construct validity relative construct validity with the Child Health Questionnaire, KIDSCREEN and GMFCS- E&R [67].

#### Caregiver satisfaction

Post intervention (T2) a custom-designed questionnaire will be used to measure satisfaction with the *Sports Stars* program. Questions will relate to group design, group content, and satisfaction with sport readiness. Outcomes will be measured on a *Sports Stars* specific eleven point Likert Scales with an additional open-ended question in each category. Answers will be reviewed by the primary investigator (GC) to determine consistent themes.

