## Methods/Design

### Study aims

The proposed study is a randomised, waitlist controlled, assessor blinded, superiority trial with two parallel groups. This study will aim to compare the effectiveness of a group-based, sports oriented physiotherapy intervention, *Sports Stars,* for ambulant school-aged children with CP, to standard care across all ICF domains. This study will also aim to gain feedback from treating physiotherapists and caregivers involved in the study to determine the acceptability of the intervention. The specific hypotheses to be tested are:

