### Treatment fidelity

Intervention therapists will be masked to baseline outcome assessments. All intervention therapists providing the *Sports Stars* intervention will be qualified physiotherapists with experience working with children with CP in a community setting. At therapist training, the detailed *Sports Stars* protocol and a sports equipment pack will be provided to all therapists to ensure that participants in all groups received consistent delivery. This includes a written week by week program of sports focussed exercises and progressions (Additional file 1) with detailed instructions and video resources that therapists can use to select predetermined difficulty levels to suit each child’s age, goals and preferences. Therapists will receive individual, face to face training in the *Sports Stars* protocol by the first author prior to the commencement of the group. Treating therapists will engage in further consultation as required with the study coordinator either by phone or in person to review the *Sports Stars* package and to discuss program content and structure prior to providing the group to participants. Each child will have features of their participation in each group session recorded by the treating therapist, including exercise type, level of difficulty and therapist observed engagement. At week three and six of the study, each therapist will undergo fidelity review and receive guidance via email through an independent, offsite co-investigator (MA) who will not be involved with assessment or treatment regarding intervention format, content, progression and data recording. Independent content analysis will determine compliance with the provided protocol. Parents of both the immediate and waitlist groups will be provided with training journals to record any therapy, including home exercises, and sport that they undertake during the study period.

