### Outcome measures and procedures

All outcomes will be collected pre-intervention, immediately post intervention and at 12 weeks post intervention by the blinded chief investigator (GC).Classification of Sample

Participants will be classified based on their severity and age to compare groups at baseline. They will be classified according to:**Gross motor function:**
*Gross Motor Functional Classification System (GMFCS-E&R)* [33]

The Gross Motor Function Classification System is an internationally recognized classification system for children and youth with CP. Participants will be classified as either classified as GMFCS- E&R I (able to walk independently at home, school, outdoors and in the community with limitations in speed, balance or coordination) or II (able to walk in most settings, however may have difficulty with distances or more challenging environments and gross motor skills like running and jumping) using the descriptors for between the child’s 6th and 12th birthday [33].b.

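### The blinded outcome assessor is also the named reviewer of the T2 Sports Stars satisfaction forms, which could reveal allocation before the T3 assessments

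*Protocol article*

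**What the plan says.** Under Study aims, the protocol article calls the trial a "randomised, waitlist controlled, assessor blinded, superiority trial with two parallel groups". Under Outcome measures and procedures, all outcomes are collected before the intervention, "immediately post intervention and at 12 weeks post intervention by the blinded chief investigator (GC"). So one person, described as blinded, assesses every child at T1, T2 and T3.

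Under Caregiver satisfaction: "Post intervention (T2) a custom-designed questionnaire will be used to measure satisfaction with the" Sports Stars program. The questions concern how the group was designed, what it contained and how ready for sport the child is, each category with an open-ended item. Then: "Answers will be reviewed by the primary investigator", in order to find common themes. The initials given there are those of the blinded assessor.

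The list of assessment times places T2 at 2 months, straight after the immediate arm's program, T3 at 5 months, and an optional T4 for the waitlist arm at about 8 months, straight after its own program.

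For the primary outcome, the COPM section says: "Three sports related goals (at least one activity and one participation focussed) will be identified by caregivers". Performance and satisfaction are then rated in an interview with the caregiver and child.

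**The concern.** A blinded assessor should have no duty that brings information about allocation before the last blinded assessment. Here the article itself assigns such a duty, so this is more than detail left to a fuller document. A family that can comment on the content of the group has attended it, and at T2 that means the immediate arm.

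At stake is the credibility of the T3 comparison. The TGMD-2 and the GMFM Challenge are scored by observation, so an assessor's expectation can enter the score. They carry the activity hypothesis (H3). The jump and throw tests are averages of three measured distances and are less exposed.

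A secondary matter is what the assessor-blinded label covers. For the COPM, blinding the interviewer does not blind the family whose views are rated.

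**Working it through.** The plan states no figure on this point, so the check sets its statements side by side.

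1. **Same person.** Outcome measures and procedures and Caregiver satisfaction give identical initials, once for the blinded collector of outcomes and once for the reviewer of the satisfaction answers.

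2. **What the form reveals.** The waitlist arm's T4 is at about 8 months, straight after an eight-week program. That program therefore starts at about 8 − 2 = 6 months, after T2 (2 months) and after T3 (5 months). At T2 no waitlist family has a program to rate. If forms go only to the immediate arm, having one identifies the arm. If they go to everyone, the answers do.

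3. **Time at risk.** From T2 to T3 is 5 − 2 = 3 months. A form handled or read in that interval, with the child identifiable, reaches the assessor before T3.

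4. **Spread within a pair.** Under Recruitment process and Randomisation, two groups of 4 to 6 children at one location are put in opposite arms by one envelope.
   - Children per pair: 2 × 4 = 8 to 2 × 6 = 12.
   - Pairs needed for 60 children: 60/12 = 5 to 60/8 = 7.5, so about 5 to 8.
   - If the assessor knows which children belong to which group (an assumption; the article does not say), one identifiable form settles the arm of both groups, and 5 to 8 forms, one per pair, would settle all 60 children.
   - Each pair has its own coin flip, so a disclosure at one location does not predict the next.

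5. **Safeguards.** The article names the reviewer of the forms but states no removal of identifiers, no delay until T3 is complete and no other handler. It does use an off-site co-investigator, uninvolved in assessment or treatment, for randomisation and for the week 3 and 6 fidelity reviews. A suitable person therefore already exists.

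6. **Which comparison is exposed.** Sample size is set on the COPM at T2. A form completed after the program bears on T2 only if the assessor sees it before or during that visit, which nothing in the article says. T3 comes after the form in every case. The linear mixed model under Analyses follows outcomes over time, so T3 COPM interviews may enter it, but the article does not make T3 the primary time point.

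7. **COPM raters.** Goals come from caregivers, and the wording on ratings points to caregivers as well. After baseline these families know whether the child attended or waited. Baseline ratings may precede that knowledge.

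**The case against.** The strongest reply is that the article does not say when the answers are reviewed, who hands out or collects the forms, or whether they carry names. Drawing out themes is a pooled task that could be done after the last T3 visit, and the handling of forms is often left to the full protocol. The sentence on outcome collection covers measures taken at three times, and a form given only at T2 may fall outside it. This stands as far as it goes: a reader might infer that T3 is unblinded as planned, and the text does not support that. It does not remove the conflict between two roles given to one person.

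Three other inferences are tempting and should not be drawn.

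- **Blinding already lost before T2.** Therapists are trained in the "protocol by the first author prior to the commencement of the group". If the first author were the assessor, allocation could be known earlier. The text at hand does not identify the first author, sends therapists' further queries to a study coordinator who is not identified as the assessor, and gives fidelity review to the off-site co-investigator.
- **The COPM contradicts the blinding claim.** Only assessor blinding is claimed, the interview with families is openly described, and families cannot be blinded in a waitlist trial of group sport. This is a matter of clear reporting.
- **A bias of known size.** No figure in the documents links the form to any outcome, and a number in COPM points would concern a different outcome from the observer-scored tests mainly at risk.

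**Conclusion.** The point holds as a conflict of roles. The blinded assessor is given a task that could reveal allocation before T3, with no safeguard stated. How far it reaches depends on handling: nobody is disclosed if the assessor sees the forms only after the last T3 visit. If identifiable forms are seen earlier, the immediate arm (30 planned) is disclosed directly, and up to all 60 children through the pairing, provided the assessor knows group membership. The exposure is mainly of the observer-scored T3 outcomes. The T2 primary comparison is not clearly affected, and neither the direction nor the size of any bias can be derived from the documents. The change is worth making because it is cheap and protects a headline feature of the design. The COPM statement is a secondary reporting improvement.

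**What to change.** 1. Under Caregiver satisfaction, state that forms are returned sealed or online to an existing team member who does not assess outcomes, for example the off-site co-investigator who already handles randomisation. State that the assessor neither distributes nor sees them until the last T3 assessment in the trial is complete. The assessor can then still do the thematic review.
2. In the COPM section, state that post-baseline ratings come from families who know the allocation, so that for the primary outcome assessor blinding covers the interviewer only.

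Both are changes of wording and routing, with no extra visits, participants or staff. The one small downside is that caregiver themes become available later.

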#### Child’s motivation and engagement within the *Sports Stars* group

To evaluate if there is a relationship between study outcomes and participant engagement, treating physiotherapists will be asked to record participants’ engagement in each component of the group intervention (warm-up, locomotor skills, object control skills, game participation and cool-down), in each therapy session using *Sports Stars* specific five point Likert Scales. Thematic analysis will be performed by to determine overarching themes.

## Adverse events

Adverse events will be reported by the treating Physiotherapist as per organisational policy. Standard organisational response and follow up will occur based on the severity of the adverse event. Any reported adverse events will be recorded by the treating physiotherapist following each session and provided to investigators at the completion of the group. They will be classified as Insignificant: no discernible injury, Minor: first aid treatment required, Moderate: medical treatment required, Major: extensive injury, or Catastrophic: resulting in death or persistent disability.

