#### Sports Stars intervention

Each group will contain between four and six participants with one lead Physiotherapist. The immediate *Sports Stars* group will receive eight, one-hour, weekly sessions (8 hours) of group-based, sports specific fundamental movement skills training, detailed in Fig. 3. These groups will introduce children to four popular Australian sports and support the development of core motor skills for transition to recreational mainstream and modified sports opportunities including *Junior Entry Point* sports programs, NetSetGo (netball), In2Cricket, MiniRoos (soccer) or T-Ball (softball/baseball). To achieve this, *Sports Stars* will focus on developing key *Body Functions* (aerobic and anaerobic fitness, muscle strength, balance and agility, and locomotor and object control) and sport-specific *Activity* skills to facilitate participation in modified sport games of soccer, netball, T-ball and cricket.

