#### Standard care comparison

Participants in the *Sports Stars* Waitlist group will receive standard care. This describes the typical intervention that a six to 12-year-old child with a diagnosis of CP would receive from their normal therapists in community, private or hospital contexts. Therapists who provided standard care will have varying degrees of experience working with children with CP. Standard care may include neurodevelopmental therapy, context-focussed therapy, strength or fitness training, or functional training. At this age, children are typically seen for 1:1 therapy, however some group therapy may also be offered. Ambulant children of this age (classified as GMFCS- E&R I-II) with CP would typically receive only 1–2 physiotherapy sessions per quarter. This may include a home program and is expected to vary between participants, however most children would receive no more than two sessions during the comparative 8 weeks of a *Sports Stars* program. Details of frequency, duration and content of any therapy session, particularly physiotherapy, will be collected via a parent log book throughout the project.

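### Adverse-event recording is described only through the Sports Stars physiotherapist, so the waitlist arm has no described capture during the randomised comparison and neither arm has any from T2 to T3

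*Protocol article*

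**What the plan says.** The section Adverse events is the only text on harms. It names the reporter: "Adverse events will be reported by the treating Physiotherapist as per organisational policy". It fixes the timing: "Any reported adverse events will be recorded by the treating physiotherapist following each session". It fixes the hand-over: the records are "provided to investigators at the completion of the group". Events are graded on a five-level severity scale. The organisational policy itself is not reproduced.

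Other sections show whom this reaches. Under Child's motivation and engagement, the same job title means the person running the program: "treating physiotherapists will be asked to record participants’ engagement in each component of the group intervention". Under Sports Stars intervention, the immediate arm "will receive eight, one-hour, weekly sessions (8 hours) of group-based, sports specific fundamental movement skills training". Under Standard care comparison, "Participants in the *Sports Stars* Waitlist group will receive standard care", delivered by the children's usual therapists, and "most children would receive no more than two sessions during the comparative 8 weeks of a *Sports Stars* program".

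A channel common to both arms already exists. Under Treatment fidelity, "Parents of both the immediate and waitlist groups will be provided with training journals". The contents listed for these journals are therapy, home exercise and sport; adverse events are not among them.

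**The concern.** Who records, when, and when the records are handed over are all defined by reference to Sports Stars sessions and the Sports Stars group. A waitlist child has neither during T1 to T3, and an immediate-arm child has neither after T2. Followed as written, the rule makes ascertainment depend on the allocated arm.

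This matters because the program consists of active sport in local parks for children whose balance and coordination are limited, as the Background describes. Falls and minor injuries are the foreseeable harms, and they also happen in everyday life. A count from the program alone cannot show whether there were more of them than there would have been without it. The T2 to T3 interval matters as well: the program is meant to lead children into community sport, and those weeks are when any such move would start to show. If the final report set out adverse events by arm, the difference would partly reflect who had a recorder present and not who was hurt.

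**Working it through.** The plan states no figure on this point, so there is none to reproduce. The check sets the sections side by side and then counts weeks.

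**Step 1: who is covered, and when**

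| Period | Immediate arm | Waitlist arm |
|---|---|---|
| T1 to T2 (program, 8 weeks) | Sports Stars therapist records after each weekly session | Usual care; no Sports Stars session, no described route |
| T2 to T3 (12 weeks) | Group finished; no described route | No described route |
| After T3 | Outside the randomised comparison | Same therapist process once the child attends the waitlist group |

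The last row follows from the timeline under Outcome measures and procedures. T4 is at about 8 months, straight after the waitlist intervention. Subtracting about 2 months for an eight-week group puts its start at about month 6, after T3 at month 5.

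**Step 2: share of follow-up with described capture**

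Inputs: 8 weekly sessions (Sports Stars intervention); T3 at 12 weeks after the immediate intervention (Outcome measures and procedures); 30 children per arm (Sample size).

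- Randomised follow-up: 8 + 12 = 20 weeks.
- Immediate arm: at most 8/20 = 40%.
- Waitlist arm: 0/20 = 0%.
- In child-weeks: at most 30 × 8 = 240 of 30 × 20 = 600 in the immediate arm, and 0 of 600 in the waitlist arm.

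If T3 is taken instead as 5 calendar months, follow-up is 5 × 52/12 = 21.7 weeks and the immediate-arm share is 8/21.7 = 37%. The conclusion is the same.

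**Step 3: what happens inside the 8 weeks**

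The rule covers any reported event and is not limited to events during the hour of the session. An injury at home that a parent mentions the following week would be recorded. The window is therefore up to 8 weeks per child and not 8 hours, but for time between sessions it relies on the family volunteering the information. No routine question is described.

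**Step 4: other routes**

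No adverse-event question is described at the T1, T2 or T3 assessments, and none in the journals or log books. Nothing shown asks the usual-care therapists to report events to the trial.

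**The case against.** Four arguments can be made against the point.

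1. *The plan makes no harms comparison.* None of the five hypotheses concerns safety, adverse events are not a listed outcome, and Analyses plans no table of them by arm. The section can be read as incident reporting for a delivered service. This stands. A reader might infer that a planned analysis is biased; the document does not support that, because no such analysis is proposed.

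2. *The source is condensed and defers to a policy that is not shown.* Children come from the client database of one state-wide service, so its policy might also reach some waitlist children's usual care, and journal fields may be set out elsewhere. This limits certainty. It does not remove the point, because the article is not silent: it states a specific rule, and that rule covers one arm.

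3. *Stronger readings go too far.* A reader might infer that everything between sessions is lost, or that the waitlist arm will have zero events. Neither follows. Between-session events can be volunteered at the next session, and for the waitlist arm the accurate statement is that no capture is described during the comparison.

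4. *The size of the problem is not a small-numbers limit.* It is tempting to say that no events in 30 children still leaves a one-sided 95% upper limit of 1 − 0.05^(1/30) = 9.5%. That is a property of the sample size. It would be the same under perfect recording in both arms, and it falls to 1 − 0.05^(1/60) = 4.9% for program-related risk if all 60 children eventually attend. It does not measure this defect.

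The remedy has a limit too: parent journals are unblinded, and immediate-arm parents see a therapist weekly, which may prompt reporting. The journals would make collection common to both arms but not free of bias.

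**Conclusion.** The point holds as a weakness in harms ascertainment. During the randomised comparison, described capture spans at most about 8 of 20 weeks in the immediate arm, with between-session events dependent on families volunteering them, and 0 of 20 weeks in the waitlist arm. Events from T2 to T3 have no described route in either arm. Data collected this way can describe the safety of the program while it is being delivered, but cannot support a statement about harms relative to standard care.

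The conclusion assumes that the treating physiotherapist in the adverse-event section is the Sports Stars therapist, as that title is used elsewhere in the article, and that the organisational policy adds no trial-wide route. If the policy or the full protocol does collect events in both arms, the point reduces to saying so in the text. It does not affect the primary COPM comparison.

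**What to change.** 1. Keep the therapist's session record and report it as safety data for the program, including sessions later attended by the waitlist arm.
2. Add one standard adverse-event item, with the existing five-level classification, to the parent journals in both arms, covering T1 to T3.
3. Have that item collected by someone other than the chief investigator, who is the blinded assessor, since an event linked to a group session would reveal allocation before T3.
4. Base any between-arm description of harms on the journal item, and note that it is unblinded parent report. With about 30 children per arm it should be descriptive.
5. If this is not adopted, state that adverse events describe the program only and support no between-arm safety conclusion.

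The cost is one extra item in an existing journal and one descriptive table. The downside is slightly more burden on parents and more minor events on record.
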